### **1.1.3 Current advice for the timing of complementary feeding in preterm infants**

The delayed early gross motor developmental progress in preterm infants should be taken into account while determining the timing of the introduction of complementary feeding. This developmental milestone may be delayed up to 3 months of corrected age. Good head control is the important developmental milestone for safe starting of solid foods. The ESPGHAN committee advised that if their baby has a reduced tongue thrust (protrusion) reflex, can sit in a stable supported position, can hold its head up well, opens its mouth, and leans forward towards the spoon the baby is developmentally ready for solid foods. These recommendations were based on the limited studies that are available in preterm infants assessing the practices of complementary foods. The only guideline relevant for introducing solid foods to preterm infants was the advice from the Department of Health in the United Kingdom (1994). This guideline recommends introducing solid foods when the preterm infant reaches a weight of 5 kg, has lost the extrusion reflex, and is able to eat from a spoon. However, it does not include an age recommendation. Observational studies in developed countries have found that solid foods have been introduced to the majority of the preterm infants prior to 4 months of corrected age. King has suggested that most preterm infants may be ready for solid foods between 5 and 8 months of uncorrected age, provided that the infant is at least 3 months of corrected age (gross motor development should enable safe eating). Palmer et al recommended that 3 months (13 weeks of corrected age) are considered as an appropriate age to start high protein, energy and nutrient rich solid foods for otherwise healthy preterm infants. Considering the corrected age the earliest born infants at 23 weeks of gestation would have an uncorrected age of 7 months, while the late preterm infants would have an uncorrected age of 4 months.

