## **5. TREATMENT OF SUBJECTS**

### **5.5 Investigational product/treatment**

The intervention group will start complementary feeding at the corrected age of 12 weeks, when gross motor development should enable safe eating. The control group will start complementary feeding at the corrected age of 17 weeks. The pattern and structure of the complementary feeding will be according to the advice of the well baby clinics in the Netherlands, using a standardized nutrition schedule.

The parents will receive information direct after the randomization about the group allocation. One week before they are assigned to start with complementary feeding, they will receive a reminder by phone. If this is not possible an email or a letter by post will be send. Parents will have one week to start with complementary feeding, either at the corrected age of 12 weeks or at the corrected age of 17 weeks. Parents will receive detailed information about complementary feeding, what kind of food to start with, how often they have to give solid foods, and some recipes. The introduction of complementary feeding is divided in 4 steps: 1) introduction of vegetables, 2) introduction of fruits, 3) introduction of cereal, and 4) introduction of a warm meal. Parents receive information when to move on to the next step. The well baby clinics and attending pediatricians are informed about the group allocation and are asked to support parents to start with complementary feeding by the time they are allocated. They also receive the information that the parents received regarding how to start with complementary feeding. In case there is a reason not starting complementary feeding at the time of allocation, parents are asked to report this and the reason why not starting in the diaries. Furthermore, the diaries will point out at what time the parents started with complementary feeding.

For the term born children (control group B) there will be no intervention with complementary feeding.

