## 10. STATISTICAL ANALYSIS

Since the sample size was not archived, the data will be interpreted with caution. Data will be analyzed on an intention to treat basis. In addition, we will also perform a per protocol analysis, taking into account the attrition rate. In case of missing values we will use multiple imputation. For the per protocol analysis, the criteria for the start of complementary feeding will be 12-13 weeks for the early group and 16-17 weeks for the late group. A p-value of 5% will be regarded as statistically significant and results will be presented with 95% confidence intervals.

Categorical data will be presented in absolute numbers and percentages. If a metric variable is normally distributed results will be shown in mean and standard deviation (sd). If a metric variable is not normally distributed median will be used with the interquartile range.

Descriptive data on BMI will be compared with the most recent Dutch growth chart. For the primary study parameter, the prevalence of obesity, the percentage of patients that develop overweight by using the IOTF will be calculated and intervention group and control will be compared including prevalence ratios with 95% confidence intervals. Furthermore, BMI and BMI z-scores between the intervention and control group will be compared as continuous variables.

The results of the questionnaires (BEBQ, CFQ, ITQoL / PedsQL, ASQ) will be analysed according to the scoring tables attached to the questionnaires. Allergy will be scored by a SCORAD form and can be presented as continuous or categorical variable. All blood and faeces results will be analysed as continuous or categorical variable. The diary results will be analysed as a continuous variable.

For all sub-objectives (as formulated in chapter 2), the intervention group and control group will be compared to determine the effect of early versus late introduction of complementary food, using a independent t-test or nonparametric test. For subgroup analysis, i.e. for children with respiratory problems or tube feeding, logistic regression will be used.

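### The per-protocol comparison selects infants by their actual start of solids and tests them at 5% without adjustment, so it can be biased in a direction and by an amount the protocol cannot fix

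*Protocol*

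**What the plan says.** Protocol section 10 sets the order of analysis: "Data will be analyzed on an intention to treat basis", followed by "In addition, we will also perform a per protocol analysis, taking into account the attrition rate". The entry rule for the second set is that "the criteria for the start of complementary feeding will be 12-13 weeks for the early group and 16-17 weeks for the late group". The same paragraph gives one 5% significance rule with 95% confidence intervals and does not exempt the per-protocol result. No covariate or weight is named for either set, and the per-protocol result is not labelled supportive.

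Section 5.5 says how the start is known and that departures are foreseen. For the timing, "the diaries will point out at what time the parents started with complementary feeding". For departures, "In case there is a reason not starting complementary feeding at the time of allocation, parents are asked to report this and the reason" in the diaries. It also says "Parents will have one week to start with complementary feeding", at 12 or at 17 weeks corrected age according to arm.

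The background describes what drives the start of solids. Section 1.1.3 cites a UK guideline that makes the start depend on weight, reflexes and the ability to spoon-feed: "introducing solid foods when the preterm infant reaches a weight of 5 kg, has lost the extrusion reflex, and is able to eat". The same section reports that most preterm infants in observational studies started before 4 months corrected age. Section 1.1.1 cites a review that wants the start individualised by nutritional status and developmental readiness. Section 4.3 cites an odds ratio of 2.5 for overweight at 18-24 months after excess weight gain between 4 and 6 months. Section 8.2 says allocation is not blinded.

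**The concern.** Randomisation makes the arms comparable as allocated. It does not do so for the subset who happened to start on time. If weight or readiness influences when parents start, and weight is also related to BMI at 2 years, then the two windows can keep different kinds of infant in the two arms. The retained groups then differ before feeding has had any effect. Reference to the attrition rate does not deal with this, because the problem is selection by start age rather than loss to follow-up.

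What is at stake is the reading of the secondary result. Section 10 says the planned sample size was not reached. A null intention-to-treat result beside a per-protocol p-value below 0.05 would then be easy to over-read.

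**Working it through.** **Scale.** The stated sample size is used for the number per arm, so it is reproduced first. Section 4.3 gives 6% versus 13%, a 0.05 level (taken as two-sided) and 80% power. With mean proportion 0.095:

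n = [1.960·√(2·0.095·0.905) + 0.842·√(0.06·0.94 + 0.13·0.87)]² / 0.07² = (0.813 + 0.347)² / 0.0049 ≈ 274.3, so 275 per group. With 5% loss, 550/0.95 = 578.9, so 579. Both agree with the protocol.

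**Assumptions (none is in the protocol).** There is no true feeding effect, and overweight is 6% in both arms. Infant weight before solids has correlation rho with BMI z-score at 2 years. The odds of being off schedule double per SD of weight (log-odds 0.69). Light infants are dropped from the early arm (start too late) and heavy infants from the late arm (start too early).

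**One-sided exclusion, 20% per arm, rho 0.3.**
- Retained per arm: 275 × 0.8 = 220.
- Mean weight among those retained: +0.128 SD early, −0.128 SD late.
- Spurious BMI z difference: 0.3 × 0.256 = 0.077.
- Standard error: √(2/220) = 0.095. Shift: 0.077/0.095 = 0.81.
- Rejection: Φ(−1.96 + 0.81) + Φ(−1.96 − 0.81) = 0.125 + 0.003 = 12.8% (simulation: 12.6%).
- Overweight: 6.42% versus 5.50%, ratio 1.17. Standard error 0.0226, rejection about 7%.

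**One-sided exclusion, 30% per arm, rho 0.4.**
- Retained per arm: 275 × 0.7 = 192.5.
- Spurious BMI z difference: 0.152. Standard error: √(2/192.5) = 0.102. Shift: 1.49.
- Rejection: Φ(−0.47) + Φ(−3.45) ≈ 32% (simulation: 32.4%).
- Overweight: 6.83% versus 5.03%, ratio 1.36. Rejection about 12%.

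**Smaller trial.** With 150 per arm and the same two cases, the standard errors become √(2/120) = 0.129 and √(2/105) = 0.138. Rejection on BMI z is then 9% and 20%; on overweight it is 6% and 9%.

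**Two-sided windows.** The windows also exclude late-arm infants who start after the upper limit and early-arm infants who start before 12 weeks. On the same mechanism these are the lighter and the heavier infants respectively. With rho 0.3 and 275 per arm:

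| Early arm drops | Late arm drops | BMI z difference | Rejection |
|---|---|---|---|
| 20% light | 20% heavy | +0.077 | 12.7% |
| 20% light | 10% heavy, 10% light | +0.038 | 6.9% |
| 15% light, 5% heavy | 10% heavy, 10% light | +0.019 | 5.5% |
| 10% light | 10% heavy, 20% light | about 0 | 5.0% |

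**A second selection model.** Here 285 per arm (600 less 5%, halved) were simulated, and start tendency had correlation b with weight.
- b = 0: no bias (4.8% rejection).
- b = 0.3, rho 0.3, 10% dropped per arm: +0.04 SD, 7.0%.
- b = 0.3, rho 0.4, 20% dropped per arm: +0.09 SD, 15.9%.
- b = −0.3 (small infants started earlier), rho 0.4, 20% dropped per arm: the difference reverses to −0.08 SD, 15.0%.
- Intention-to-treat stayed at 4.6-5.6% in every scenario.
- Adjusting the per-protocol comparison for pre-start weight returned rejection to 4.6-5.5%. In this model weight was the only common cause.

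**The case against.** The strongest reply is that this caution applies to any per-protocol analysis, and the plan already treats it as secondary. Intention-to-treat is listed first, section 10 promises cautious interpretation, and the Summary says the main result will be read as an association. Covariates for a supplementary set are often left to a statistical analysis plan. The 5 kg guideline is cited background, not a rule of this trial: parents receive an allocated date, a reminder and a standard schedule. All of this stands, and it limits the weight of the point. It does not remove it, because the protocol itself fixes the selection rule and the 5% test.

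A reader might infer more, and the documents do not support it:

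- *That the bias must favour the hypothesis that early feeding leads to more overweight.* The direction is conditional. Individualising by nutritional status could equally mean that smaller infants start sooner, and the sign then changes.
- *That it arises wherever the windows are set.* The table shows that its size depends on what each limit removes. If 16-17 weeks ends at exactly 17 weeks, late-arm infants who used the one-week period in section 5.5 are excluded, which changes the size and perhaps the sign. Sections 5.5 and 10 need to be reconciled on this.
- *That 32% is the error rate of the trial's main result.* It belongs to BMI z-score in the per-protocol set under strong assumptions. Overweight is much less affected.
- *That non-adherence would cut a 7-point intention-to-treat effect to 2.8-4.2 points.* That needs every off-schedule infant to receive the other arm's full effect. An early-arm infant who starts at 14 weeks is off schedule without having crossed over.

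**Conclusion.** The point holds in conditional form. As written, the per-protocol comparison conditions on a post-randomisation behaviour that the protocol's own background relates to weight and readiness, and it carries a nominal 5% test whose true error rate is not controlled. Plausible inputs give anything from no inflation to roughly 12-32% on BMI z-score and 7-12% on overweight at 275 per arm, and the sign is not determined. These figures rest on assumed non-adherence, an assumed weight-start relation and an assumed weight-BMI correlation. The main conclusion is safe so long as it rests on intention-to-treat. The change is worth making, but it does not threaten the trial.

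**What to change.** Amend section 10, or the statistical analysis plan, in three ways:

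1. State that intention-to-treat decides and that the per-protocol result is supportive only and cannot override it.
2. Adjust the per-protocol comparison for weight and BMI measured at the visit before solids (section 3), gestational age and centre. Express weight as a score for age at measurement, since section 3 gives no fixed age for that visit. This removes bias only to the extent that these variables capture why parents departed from schedule; unmeasured readiness would remain.
3. Add a complier-average (instrumental-variable) estimate for the overweight risk difference and BMI z-score, with randomised arm as instrument and diary start age as exposure. In its simplest form this is the intention-to-treat difference divided by the between-arm difference in mean start age, giving an effect per week. State the assumption that allocation affects BMI only through start age.

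The cost is some wording and two models on data already planned for collection. The complier-average estimate will have wider confidence intervals than the per-protocol comparison, and its exclusion assumption cannot be tested. It could fail, for example, if allocation in this open-label trial changed other feeding habits.

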### 8.3.9 Microbiota – Collecting faeces – Extra in this study

Parents of all preterm children in group 2a are asked to collect faeces at home at three different time points:

- First sample: 10-11 weeks post term (before the start of complementary feeding)
- Second sample: 15-16 weeks post term (after the ‘early-group’ has started complementary feeding)
- Third sample: 20-21 weeks post term (after both ‘early-group’ and ‘late-group’ have started complementary feeding)

To evaluate if the microbiota change due to the start of complementary feeding, samples before and after the start of complementary feeding will be compared. The late group will function as a ‘control group’ when analyzing the second sample, since the ‘early-group’ has already started with complementary feeding, whereas the ‘late-group’ has not yet started with complementary feeding.

Parents are asked to collect three samples of the faeces at home by using a fecal swab. The fecal swab is inserted in the stool in the diaper, and afterwards the fecal swab is transferred into a tube.

---

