### **11.4 Benefits and risks assessment, group relatedness**

The burden and risks associated with participation to this study are minimal. The benefits of starting early complementary feeding are well described by King. King suggested that it is not necessary to wait for lip seal to develop and tongue protrusion to diminish before

weaning. In fact, premature children may only mature with the aid of weaning. Furthermore, some infants may develop rapidly with increasingly textured food. There is evidence for not starting complementary feeding before 3 months corrected age, because motor development necessary for safe and successful transition to solid foods may not have been achieved until at least 3 months. For that reason, none of the children will start complementary feeding before 3 months of age corrected age. From data on term infants it seems likely that the later a preterm infant is introduced to new tastes, the less likely they are to accept a wide variety of foods. King also puts forward that there is no evidence that preterm infants are more likely to develop atopic diseases due to immaturity of the gut and immune system.

For the primary outcome we would like to determine BMI at the age of 2 years. Additionally, we would like to determine BMI before the start of complementary feeding and at the age of 1 year. Ideally, we would like to combine these hospital visits with regular visits in the follow-up of the preterm infants.

Furthermore, we will ask parents to collect faeces at home at three different timepoints. The faeces will be analysed to evaluate if the microbiota change due to the introduction of complementary feeding.

In conclusion, we would like to obtain information before the start of complementary feeding and at the age of 1 and 2 years. This means three extra hospital visits, depending on the arrangement for the follow-up of preterm infants in the different hospitals. Whenever possible, visits for the study will be combined with regular visits. The risks associated with this study are minimal. There will be no benefit for the individual participating in this study. To determine correlations between height, weight, BMI, and eating behaviour in preterm infants it is important to perform this study in this age category.

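### The late group's per-protocol window (16-17 weeks) does not match its start instruction (17 weeks, with one week to start), while the early group's window runs forward from its allocated age

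*Protocol*

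**What the plan says.** Protocol Section 5.5 fixes the two allocated ages. For the early arm it reads: "The intervention group will start complementary feeding at the corrected age of 12 weeks". The late arm is set five weeks later: "The control group will start complementary feeding at the corrected age of 17 weeks". Section 5.5 then describes how families are prompted: "One week before they are assigned to start with complementary feeding, they will receive a reminder by phone". One allowance covers both groups, worded first for the early arm: "Parents will have one week to start with complementary feeding, either at the corrected age of 12 weeks". The same sentence extends it to the late arm at its own allocated age. The actual start date is to be read from the parents' diaries.

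Section 10 makes intention to treat the basis and adds a per-protocol analysis, whose adherence rule reads: "the criteria for the start of complementary feeding will be 12-13 weeks for the early group and 16-17 weeks for the late group". It does not explain why the two windows sit differently around their allocated ages, or whether the limits are exact ages or completed weeks.

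Two other places bear on the windows. Section 11.4 says that "none of the children will start complementary feeding before 3 months of age corrected age", and Section 2 equates three months with 12 weeks. Section 2 also treats 27 weeks after birth, which an infant born at 30 weeks reaches at 17 weeks corrected age, as the outer limit for starting.

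**The concern.** A per-protocol criterion should describe what families were told to do. Here the early criterion does, and the late one is moved a week earlier. A start ahead of the allocated age is therefore tolerated in one group only, and on one reading some late families who followed the instruction are dropped.

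Three things are at stake, all within the per-protocol analysis:

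- **Who is selected.** Allocation is open and the start date is a parental decision made after randomisation. A criterion that forgives early starts in one arm only selects the two sets by different rules.
- **The contrast.** The arms are planned five weeks apart, which Section 2 itself acknowledges looks small. The accepted windows are centred closer together than that.
- **The microbiota comparison.** Section 8.3.9 uses the late group as the control for the sample at 15-16 weeks post term, on the ground stated there: "whereas the ‘late-group’ has not yet started with complementary feeding". A late infant who starts at 16+0 to 16+6 counts as per protocol, yet may already be on solids if that sample is taken during week 16.

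**Working it through.** **Inputs.** Allocated ages 12 and 17 weeks corrected, and one week to start (Section 5.5). Per-protocol windows 12-13 and 16-17 weeks (Section 10). Ages below are weeks+days.

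**Planned contrast.** 17 − 12 = 5 weeks. With the one-week allowance counted from the allocated age, the instructed weeks are 12+0 to 12+6 and 17+0 to 17+6. Their mid-points are 12.5 and 17.5, again 5 weeks apart.

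**Windows against instructed weeks.** Section 10 can be read in two ways.

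| | Exact ages | Completed weeks |
|---|---|---|
| Early window | 12+0 to 13+0 | 12+0 to 13+6 |
| Late window | 16+0 to 17+0 | 16+0 to 17+6 |
| Early instructed days inside window | 7 of 7 | 7 of 7 |
| Late instructed days inside window | only 17+0 | 7 of 7 |
| Days accepted before allocated age, early | 0 | 0 |
| Days accepted before allocated age, late | 7 (16+0 to 16+6) | 7 (16+0 to 16+6) |
| Whole days accepted after instructed week, early | 0 | 7 (13+0 to 13+6) |
| Whole days accepted after instructed week, late | 0 | 0 |
| Mid-points, weeks | 12.5 and 16.5 | 13 and 17 |
| Mid-point contrast | 16.5 − 12.5 = 4 | 17 − 13 = 4 |
| Smallest gap between windows | 16 − 13 = 3 weeks | 16 − 14 = 2 weeks |

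Two results hold under both readings: the late arm accepts seven days before the allocated age and the early arm none, and the mid-points are 4 weeks apart. The exclusion of late infants who start at 17+1 to 17+6 holds only under exact ages.

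**A third reading.** Suppose the allowed week is counted from the reminder, one week before the allocated age. The instructed weeks become 11 to 12 and 16 to 17. The late window then fits, but the early window (12-13) meets its instructed week only at 12+0, and starts between 11 and 12 weeks would contradict Section 11.4.

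No single one-week rule applied to both arms matches both windows under any of these readings.

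**The case against.** The strongest reply is that the protocol counts in completed weeks. Table 1 in Section 2 supports this. Birth at 35 6/7 weeks is 4+1 before 40 weeks, so a start at 12 weeks corrected is 16+1 after birth and is printed as 16 weeks; a start at 17 weeks is 21+1 and is printed as 21. On that convention the late window reaches 17+6 and every late infant who follows the instruction is kept. This stands, and it is why the exclusion is stated here only as conditional. It does not remove the week accepted before the allocated age.

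The second reply is that the asymmetry may be deliberate. Section 11.4 gives a reason not to extend the early window backward, and the outer limit in Section 2 gives a reason not to extend the late window forward. That is plausible, and it means a forward window in both arms cannot be assumed to be what was intended. But Section 10 does not give this reasoning, and if it applies, the week allowed after 17 weeks in Section 5.5 is itself in tension with Section 2.

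The third reply is that the analysis is supplementary and the diaries hold the start dates, so another window can be applied at any time. That is true and limits the weight of the point. A criterion changed once results are known is, however, less convincing than one settled beforehand.

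**Conclusion.** The inconsistency is real and confined to the per-protocol analysis. On the exact-age and completed-week readings alike, the late arm counts starts up to seven days before allocation as adherent, the early arm does not, and the window mid-points are 4 weeks apart rather than 5. If the limits are exact ages, late infants who start at 17+1 to 17+6 as instructed are also excluded.

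A reader might infer more, and the protocol does not support it:

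- **That 6 of 7 adherent late infants (86%) are lost.** This needs exact ages and starts spread evenly over 17+0 to 17+6. The protocol states neither.
- **That the realised contrast falls by a fifth.** The 4 weeks describes the windows, not the infants. It would be the realised contrast only if starts were centred in each window. If families follow Section 5.5 and completed weeks are meant, the contrast stays at 5 weeks.
- **That the selection is related to BMI.** Parents might start early because of appetite or growth, but the protocol offers no evidence of it here.
- **That the main comparison is affected.** Neither the intention-to-treat analysis nor the sample size calculation uses these windows.

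The number of infants misclassified cannot be computed from the protocol.

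**What to change.** Reconcile Sections 5.5 and 10 with each other, and with Section 2 (outer limit for starting) and Section 11.4 (no start before three months corrected age). Which start rule is confirmed is for the investigators; this review takes no position on it.

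Then, in Section 10:

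- define per-protocol adherence in weeks plus days, with both end points stated;
- use one rule for both arms that matches the confirmed start instruction;
- take the start date from the diary in which parents record the first solid food;
- report starts outside the window as deviations by arm, including starts before the allocated age in either arm.

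The cost is about a sentence in Section 10, plus whatever wording the reconciliation requires elsewhere. No new data are needed, and the sample size and intention-to-treat analysis do not change.
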